#### Normative Information

Normative information will either be included or omitted in addition to the calls-to-action. This normative message will read *“In similar studies, the majority of people decided to donate some of the money should they win it,”* followed by a question about the participants’ willingness to donate (see Table 1). Although the normative imessage could be stronger than the one suggested (i.e., “*In*
***this***
*study, the majority of participants decided to donate”*), it would risk being deceitful if it turned out to be inaccurate. The one we are proposing is subtler but non-deceitful, as it is based both on our pre-study results and various previous studies that showed that a substantial number of participants actually decides to donate. For example, in Nilsson et al. (2016) study, 60 and 62% of the participants donated some of the money they earned in the study, while in Reed et al. (2007) study, 90% of the participants decided to donate either time or money.

Apart from these measurements, participants will also be asked to provide some basic demographic information such as age, gender, education, nationality, ideology, and previous donations.

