### The Determinants of Charitable Behavior

In this protocol, charitable behavior (CB) refers to the measurable actions of supporting a charity through donating money or time. To construct an intervention that influences CB, it is first necessary to identify its potential determinants. CB has often been examined in the context of the Theory of Planned Behavior (TPB; Ajzen, 1985, 1991). In the TPB, the immediate causes of any behavior are (1) intentions to perform that behavior and (2) the actual control one has over performing it. In turn, behavioral intentions result from individuals’ attitudes, social norms and perceived behavioral control. Indeed, some studies found that these TPB variables are good predictors of CB. For example, van der Linden (2011) found that attitudes, perceived behavioral control, past behavior and moral norms significantly predicted charitable giving intentions. Smith and McSweeney (2007) reported similar results, but identified injunctive norms as an additional predictor of charitable giving intentions. Thus, one way to increase CB is to influence one or more of its immediate causes, such as changing attitudes and referencing a social norm.

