## Materials and Equipment

### Participants

The number of participants needed when conducting the study according to this protocol mostly depends on the desired effect size we would like to be able to detect and the statistical power we would like to achieve. For example, using the multivariate analysis of variance, if we would like to achieve a power of at least 1−β = 0.90 to detect small effects (*f*^2^ = 0.02) with the probability of *Type I* error set at α = 0.05, we would need a sample size of *N* = 439 as calculated using *G^∗^Power 3* (Faul et al., 2007). However, given that it is expected that researchers will have to omit some participants whose scores do not meet the criteria for individualizing and binding groupings which will be determined from the data [due to calls-to-action not being (in)congruent enough with their moral views], it would be advisable to further increase the number of participants by 20%. Therefore, the ideal final sample would be around *N* = 527. Of course, if one would, for example, like to study the effects of (in)congruent calls-to-action and norms on donations to two different charity causes separately (e.g., those hypothesized to be more in line with liberals’ and conservatives’ values), one would need to double this number. On the other hand, if one is willing to the accept somewhat lower power of 1−β = 0.80, that is usually accepted in psychological research, one would need the sample size of *N* = 344, or around *N* = 412 if one decides to increase it by 20%.

The recruitment of participants can take place online. For example, in order to obtain a mixture of conservative and liberal participants, the link to the survey can be disseminated through different conservatively and liberally oriented Facebook groups (see Table A1 in Appendix A). Other online platforms where it is relatively easy to approach the users of different ideological positions can be also utilized, such as Reddit, Twitter etc.

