## Statistical Analysis

To test for the effects of moral congruence of the calls-to-action, descriptive social norms, and their interaction on donations of time and money, a multivariate analysis of variance (MANOVA) will be conducted. In the same analysis, a test for the moderating effect of moral internalization on the congruence of the calls-to-action will also be conducted. This approach allows researchers to account for potential relationships between our dependent variables, and to test whether the experimental manipulations influence participants on a combination of different types of donations (Field, 2009). Furthermore, in comparison with univariate ANOVA, that requires several individual tests, using MANOVA reduces the probability of making a *Type I* error.

To test whether attitudes toward CB mediate the effects of (in)congruence of the calls-to-action on CB, and whether descriptive social norms mediate the effects of normative information on CB, a mediation analysis will be conducted. This can be done by using the bootstrapping method developed by Preacher and Hayes (Hayes, 2013). This is because previous approaches related to this analysis, such as the causal step approach (Baron and Kenny, 1986), have been criticized for lack of power, the underlying assumptions and inability to directly evaluate potential mediation (MacKinnon et al., 2002).

To determine if people’s moral foundations can be predicted from their Facebook data, various machine learning algorithms can be employed^5^. However, as this part of the study is exploratory and primarily concerned with maximizing prediction accuracy, we cannot specify the exact algorithm which will be reported. Various models and approaches can be tried out, choosing the one that exhibits the least amount of generalization error, i.e., the one that performs best on unseen data, which will be determined through cross-validation. Some possible approaches are LASSO (*Least Absolute Shrinkage and Selection Operator*) regression, multiple linear regression on clustered data and principal component regression^6^ (James et al., 2013; Kosinski et al., 2016).

The analyses can be conducted using the R language (R Core Team, 2017). For implementing the various machine learning algorithms, we will use existing packages, such as glmnet (Friedman et al., 2010), irlba (Baglama et al., 2017) and topicmodels (Grün and Hornik, 2011).

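### Previous donations and ideology are collected before randomisation but appear in neither the MANOVA nor the mediation analyses: some precision is given up, and mediator-outcome confounding is left unaddressed

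*Protocol article*

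**What the plan says.** - **Collection.** At the end of Normative Information: "participants will also be asked to provide some basic demographic information such as age, gender, education, nationality, ideology, and previous donations".
- **Timing.** In the Stepwise Procedure the demographic questionnaire is step 3 and random assignment is step 4. These items are therefore proper baseline variables.
- **Prognostic value.** The Determinants of Charitable Behavior cites a study in which "attitudes, perceived behavioral control, past behavior and moral norms significantly predicted charitable giving intentions". Changing Behavior by Changing Social Norms describes studies that tested norms while controlling for past behaviour, among other things.
- **Confirmatory model.** The Statistical Analysis section names a MANOVA of time and money donated on congruence, norm and their interaction. It adds that "a test for the moderating effect of moral internalization on the congruence of the calls-to-action will also be conducted" in the same analysis.
- **Mediation.** The same section plans bootstrap mediation through attitudes (for congruence) and through perceived descriptive norms (for normative information). It names no covariates and gives no use for previous donations or ideology.
- **Sample size.** Participants sets the size for a multivariate analysis of variance "with the probability of *Type I* error set at α = 0.05": "we would need a sample size of *N* = 439" at 90% power, and for 80% power "one would need the sample size of *N* = 344".

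**The concern.** The authors describe past behaviour as a predictor of giving, cite work that adjusted for it and collect it before assignment. The named models then do not use it.

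Two things are at stake, and they differ in kind:

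1. **MANOVA.** Variance that past giving and ideology could explain stays in the error term. That costs power and widens intervals for every experimental effect.
2. **Mediation (aim iv).** Attitudes and perceived norms are measured, not assigned. Someone who has given before may both think better of giving and be more willing to give. An unadjusted mediator-to-outcome path could pick up that shared cause and be read as a mechanism.

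**Working it through.** **Step 1: reproduce the plan's figure.** Inputs from Participants: α = 0.05, f² = 0.02, power 0.90 and 0.80. There are two outcomes (time, money), p = 2, and k = 6 cells. Power for the Pillai trace with hypothesis df q:

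- s = min(p, q); df1 = p·q; df2 = s(N − k − p + s); noncentrality λ = f²·s·N; noncentral F.

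With q = 3 and N = 439: s = 2, df1 = 6, df2 = 2(439 − 6 − 2 + 2) = 866, λ = 0.02 × 2 × 439 = 17.56, power 0.900. With N = 344: λ = 13.76, power 0.800. Both stated sizes reproduce exactly, with no covariates. (Three outcomes with q = 2 give the same N.)

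**Step 2: the tests the design actually contains, N = 439, unadjusted.**

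- Norm, q = 1: df 2 and 432, λ = 0.02 × 1 × 439 = 8.78, power 0.757.
- Congruence, q = 2: df 4 and 866, λ = 17.56, power 0.936.

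**Step 3: add covariates.** If they explain a share R² of the outcomes' residual variance, f² becomes 0.02/(1 − R²), and c covariate df come off: df2 = s(N − k − c − p + s). The document gives no R², so the range is an assumption. The table charges c = 10.

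| Assumed R² | 1/(1 − R²) | Norm, 1 df | Congruence, 2 df | 3-df test behind N = 439 |
|---|---|---|---|---|
| 0 (no covariates) | 1.00 | 0.757 | 0.936 | 0.900 |
| 0.02 | 1.02 | 0.766 | 0.941 | 0.907 |
| 0.05 | 1.05 | 0.779 | 0.948 | 0.917 |
| 0.10 | 1.11 | 0.802 | 0.959 | 0.932 |
| 0.20 | 1.25 | 0.849 | 0.977 | 0.959 |
| 0.30 | 1.43 | 0.895 | 0.989 | 0.979 |

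Example, norm test at R² = 0.10: λ = 8.78/0.90 = 9.76, df2 = 422, power 0.802. Charging 2 df instead of 10 changes power by no more than about 0.0001. In terms of N, the 3-df test at 90% power needs 396 instead of 439 at R² = 0.10 and 352 at R² = 0.20. Interval width scales with √(1 − R²): 0.95 and 0.89.

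**Step 4: the mediation path.** Take an illustrative case, all values assumed: N = 439, a two-arm exposure that shifts the mediator by a = 0.3, a true mediator-to-outcome effect of zero, and a baseline variable correlated r with mediator and outcome (unit variances given exposure). The unadjusted path then has expectation r × r, and the spurious indirect effect is a·r²:

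- r = 0.2: 0.3 × 0.04 = 0.012
- r = 0.3: 0.3 × 0.09 = 0.027
- r = 0.4: 0.3 × 0.16 = 0.048

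In simulation, the 95% interval for the indirect effect wrongly excluded zero in about 10–13%, 39–40% and 80% of runs respectively. With the baseline variable in both equations the rate was about 4–5% throughout. This shows how the bias would arise and how large it could be; the document supplies no value of r.

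**The case against.** The strongest reply is that this is an omission and not an error. A covariate list often sits in an analysis plan, a condensed article need not give one, and nothing in the Statistical Analysis section excludes covariates. That much stands: nothing there is wrong or contradictory. But the section names the model and its terms, and the sample size matches a covariate-free analysis. The point is therefore a concrete improvement to a stated analysis, not a complaint about missing detail.

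Other parts of the reply also stand:

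- **Validity.** A reader might infer that the MANOVA is biased or that N = 439 is wrong. Neither follows. Random assignment protects the unadjusted comparison, and 439 is exact for a 3-df test of this form.
- **Size of the gain.** A reader might take the 11–43% gain in effective sample size at R² = 0.10–0.30 as the expected benefit. The document reports no R². At 0.02–0.05 the norm test gains only about 0.01–0.02 in power.
- **Choice of test.** The norm test has the lowest power of those shown. Its 0.757 arises because 439 corresponds to a 3-df test, which is a separate matter. The congruence test starts at 0.936 and has less to gain.
- **Mediation.** That the indirect effect is inflated is plausible but not documented. Both exposures are randomised, so only the mediator-to-outcome path is open to confounding.
- **Scope.** Not every baseline measure is ignored. Moral internalization is in the model as moderator, and the moral foundations scores define congruence. Ideology overlaps with those scores, so what it adds may be modest.

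**Conclusion.** The point holds as a low-cost improvement. Previous donations and ideology are available before assignment, the protocol itself gives reason to think past giving is prognostic, and the named analyses use neither.

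For the MANOVA the consequence is lost precision, not lost validity. It is slight if R² is 0.02–0.05 and worth having from about 0.10, where the norm test passes 80% power at N = 439. These figures assume f² = 0.02 on the unadjusted scale and an R² that applies equally to both outcomes.

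For the mediation analyses the matter touches validity, because the mediator is not randomised. The likely direction of bias is upward, if past givers both hold better attitudes and give more. The document does not establish that direction or its size. Adjusting for measured past giving would reduce this confounding but would not remove confounding by unmeasured causes.

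**What to change.** Add to the Statistical Analysis section:

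- The confirmatory analysis is a MANCOVA with the experimental terms already named plus previous donations and ideology as pre-specified covariates. Age and gender are optional.
- Nationality enters only if collapsed in advance to a few levels, since open online recruitment could produce many sparse categories. It should not be treated as survey language: translation is described for the pre-study, and the document does not say that language follows nationality in the main study.
- The same covariates enter both equations (mediator and outcome) of each mediation model. The report states that confounding by unmeasured causes remains possible.
- The unadjusted MANOVA is reported as a sensitivity analysis.

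The covariates and their coding should be fixed before the data are seen, so that they cannot be chosen by result. The sample size need not change. The cost is a few sentences and a few degrees of freedom; even ten covariate df change the required N by at most one participant.

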### The Dependent Variables

#### Attitudes Toward CB

In line with proposals for constructing TPB questionnaires (Ajzen, 2006), attitudes will be assessed with several semantic differential scales. Participants will respond to the following question: “I believe that making a donation to a described charity in terms of money or time would be:” (1) unpleasant – (7) pleasant, useful – useless, satisfying – unsatisfying, favorable – unfavorable, positive – negative, considerate – inconsiderate, pointless – worthwhile, and bad – good. Items will be scored such that higher scores indicate a more positive attitude toward CB. The internal consistency of a similar scale was shown to be α = 0.93 (Smith and McSweeney, 2007).

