#### Changing Behavior by Changing Attitudes

An intervention aimed at increasing CB may focus on changing people’s attitudes toward CB. One promising way of doing this is by using the assumptions of Regulatory Fit Theory (Higgins, 2005). According to Regulatory Fit Theory (RFT), it is possible to increase the effectiveness of a persuasive appeal by framing the arguments of a persuasive message in a way that fits one’s psychological characteristics. This could include motivational orientation (Updegraff et al., 2007), personality (Hirsh et al., 2012) or moral characteristics (Feinberg and Willer, 2013). Regulatory fit is hypothesized to shift attitudes through three intertwined mechanisms: by making the recipient ‘feel right’ during the message reception, by increasing the recipient’s strength of engagement with the message, which contributes to processing fluency, and by influencing elaboration likelihood (Cesario et al., 2008).

What psychological characteristics are most relevant in the context of CB? It seems that an individual’s morals play a significant role. For example, Smith and McSweeney (2007) and van der Linden (2011) showed that personal moral norms are one of the strongest predictors of CB. Furthermore, Aquino and Reed (2002) moral identity internalization, or degree to which moral traits are central to one’s self-concept, has been shown to influence: (a) type of charitable donations (time versus money), (b) donation intentions, (c) actual donations, and (d) emotions experienced during donations. Those who feel that morality is central to their self-concept: (a) prefer donating time instead of money, (b) show greater intentions to donate money, (c) are willing to actually donate more money, and (d) experience more positive donation related emotions than those who are lower on moral identity (Reed et al., 2007; Winterich et al., 2012). This evidence makes a strong case for the importance of individual morals in predicting CB.

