#### Charitable Behavior

Since CB is not a unidimensional construct but can be classified into three main categories - helping a stranger, giving time and giving money (Charities Aid Foundation [CAF], 2017) – in this study we decided to measure CB in two different ways:

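### The attitude mediator asks about money and time in one stem, so mediation specific to one form of giving cannot be identified and may be attenuated by an unknown amount

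*Protocol article*

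**What the plan says.** The section Attitudes Toward CB (CB is charitable behavior) fixes the wording of the mediator. Respondents complete eight semantic differentials under the single stem "I believe that making a donation to a described charity in terms of money or time would be". No item refers to money alone or to time alone.

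The section Charitable Behavior takes a different line on the outcome. It opens "Since CB is not a unidimensional construct but can be classified into three main categories" and continues "in this study we decided to measure CB in two different ways". Time is then a 7-point item on interest in volunteering, and money is an amount out of a 50 euro/pound gift card. The Stepwise Procedure randomises the order of these two questions.

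For analysis, the Statistical Analysis section tests the two donation measures jointly in one MANOVA, partly "to test whether the experimental manipulations influence participants on a combination of different types of donations". The mediation analysis there, like aim (iv), names its outcome only as CB. The article defines no composite CB score.

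**The concern.** The stem holds two attitude objects and allows one answer. A respondent who feels differently about giving money and giving time must blend them or choose one, and nothing in the data will show which. No later analysis can recover this.

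The protocol gives its own reasons to expect a difference. It separates the outcomes because giving has more than one dimension. Its introduction reports that people high on moral internalization "prefer donating time instead of money", and internalization is the moderator in aim (iii). In addition, the norm sentence mentions only money and is shown before the attitude items. It could lead respondents in the norm arms to read the stem as being about money; that is an inference, but the single stem leaves no way to check it.

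Aim (iv) is what is at stake. If a call changes mainly one attitude, part of the mediated effect on the matching outcome can be lost from the indirect path and reappear as a direct effect. A weak or null mediation result could then mean either that attitudes do not mediate or that the other attitude was mixed in.

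**Working it through.** **No figure to reproduce.** The article gives no path coefficients, no size for the indirect effect and no power for the mediation analysis. The check therefore asks how far a combined answer could distort an indirect effect. The quantities w, c and ρ below are assumptions, not document values.

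**Model.** Let A_m and A_t be the attitudes to giving money and giving time, with equal residual variance and residual correlation ρ. The call shifts A_m by a and A_t by c·a. Money given depends on A_m only, with slope b, so the true indirect effect is a·b. The recorded answer is M = w·A_m + (1−w)·A_t.

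- Shift in M: a·[w + (1−w)c]
- Slope of money on M, given the call: b·[w + (1−w)ρ] / [w² + (1−w)² + 2w(1−w)ρ]
- Measured/true indirect effect: the product of the two bracketed factors

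**Equal weighting, w = 0.5.** The slope factor is (0.5 + 0.5ρ)/(0.5 + 0.5ρ) = 1, so the ratio is 0.5 + 0.5c whatever ρ is. This gives 0.50 for c = 0, 0.75 for c = 0.5 and 1.00 for c = 1.

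**Other weights, ρ from 0 to 0.9.**

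| Weight on money, w | Only the money attitude moves (c = 0) | c = 0.5 | Both move equally (c = 1) |
|---|---|---|---|
| 0.25 | 0.10 to 0.24 | 0.25 to 0.60 | 0.40 to 0.96 |
| 0.50 | 0.50 | 0.75 | 1.00 |
| 0.75 | 0.76 to 0.90 | 0.89 to 1.05 | 1.01 to 1.20 |
| 1.00 | 1.00 | 1.00 | 1.00 |

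Worked example for w = 0.25, ρ = 0, c = 0: shift factor 0.25; slope factor 0.25/(0.0625 + 0.5625) = 0.40; ratio 0.25 × 0.40 = 0.10.

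The same formula serves volunteering interest if w is read as the weight on time. If respondents read the stem wholly as money (weight on time 0), the ratio for the time outcome is c·ρ. What protects one outcome can therefore harm the other.

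**Simulation check.** With equal weights, n = 1,000,000, a = 0.4 and b = 0.5, the true indirect effect is 0.20. For ρ of 0, 0.5 and 0.8:

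- c = 0: ratio 0.50 to 0.51, direct effect about 0.10, total about 0.20. The lost half has moved to the direct path.
- c = 1: ratio 1.00 to 1.01, direct effect about zero.

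**Are the two forms of giving interchangeable?** In the pre-study (N = 50), 86% would give money and 78% were interested in volunteering: 0.86 × 50 = 43 and 0.78 × 50 = 39. At least 43 − 39 = 4 people answered the two differently. This is modest evidence, and it concerns willingness rather than attitude.

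**Reliability of a half-length scale.** Spearman-Brown from the quoted alpha: 0.5 × 0.93/(1 − 0.5 × 0.93) = 0.465/0.535 = 0.869. This assumes that the alpha, reported for a similar scale whose length is not given, applies to eight items.

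**The case against.** The strongest defence is that the stem matches the construct. The protocol states that "charitable behavior (CB) refers to the measurable actions of supporting a charity through donating money or time", and aim (iv) names attitudes toward CB as the mediator. A general attitude to a broadly defined behavior, set beside a joint test of both donations, is coherent. Mediation specific to money or to time is a finer question than the aim poses. This stands as far as it goes, but the outcome is recorded only as two separate items on different scales.

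The protocol's expectation also lies close to the case with no loss. Anticipated Results expects better attitudes to raise both time and money given. Apart from the norm line, the call texts ask for support in general terms and mention neither money nor time, so no feature of the calls points to a shift in one attitude alone. The reported preference for time among people high on internalization is a difference between people; it does not show that a call moves one attitude and not the other. These points limit the likely size of the problem but do not remove the ambiguity.

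A reader might infer that the plan analyses money and time separately and so contradicts itself by merging them in the mediator. The documents do not support this: the two are measured separately, but the stated test is a joint MANOVA and the mediation outcome is named only as CB.

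**Conclusion.** The concern holds as a limit on what aim (iv) can show. The stem is fixed verbatim, it merges two attitudes that the protocol has reason to keep apart, and the merger cannot be undone after data collection. An indirect effect specific to one form of giving may be attenuated by an amount that the documents do not determine.

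A reader might infer that the indirect effect is simply halved. That needs three conditions together: equal weighting, a shift in one attitude only, and an outcome driven by that attitude alone. None is stated in the documents. When only the relevant attitude moves, the ratio on the grid above runs from 0.10 to 1.00. Over the whole grid it runs from about 0.10 to 1.20, so the bias need not even be downward when both attitudes move. With equal weights and equal shifts nothing is lost.

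No figure in the protocol is wrong, and the randomised total effects on donations are untouched. This is a modest measurement weakness, worth correcting because it is cheap before launch and irreparable afterwards.

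**What to change.** Before launch, replace the single stem with two: *donating money to this charity would be* and *giving your time to this charity would be*. Put the same four adjective pairs under each, so that the total stays at eight items and adjective content is not confounded with the form of giving. In the mediation analysis, use the money scale for money given and the time scale for volunteering interest. Keep the mean of the two scales as the general attitude toward CB, so that the broad question in aim (iv) can still be answered.

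The cost is a wording change and no extra items. Each scale has four items instead of eight, with reliability of about 0.87 under the assumption stated above, and draws on four different adjective pairs rather than eight. The two mediator scores are likely to be correlated, which should be kept in mind when the two mediation results are compared.
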